### Recruitment {15}

Participants will be enrolled through being scheduled for surgical procedures, such as laparoscopic gastrointestinal surgery for cancer. For prospective recruitment, an information sheet will be provided regarding the trial objectives, workflow, and randomization procedures. Prior to the procedure, the participant will provide written informed consent. In cases where the participant is unable to do so, a legally authorized representative or caregiver will be contacted to provide consent on behalf of the participant, in accordance with the GCP guidelines.

Preoperative visits will be conducted; and the inclusion and exclusion criteria will be strictly employed. Participants who meet all the eligibility criteria and provide written informed consent will be eligible for enrollment. A trained research team will recruit participants and use standard randomization procedures, to assign them to the study population on the preoperative day. The anesthesiologist will only be notified of this assignment the day after the participant is admitted to the ward.

## Assignment of interventions: allocation

### Sequence generation {16a}

Post-initiation of the study, each clinical trial site will continuously screen eligible participants and enroll them in the trial. Participants will be randomly assigned. The study employed block randomization with center stratification, where each center competed for inclusion. The electronic data capture (EDC) system generated the randomization. The participants will be assigned to two cohorts, as per a 1:1 ratio, on the preoperative day. To balance the variables, we will stratify the participants according to the following factors: age, surgical position, area of the clinical trial site, operative time, and the anesthetic drug administration and method.

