### Intervention description {11a}

Preoperatively, the participants in both cohorts will fast for 8 h and not use any sedatives or analgesics. On arrival at the ward/operating room, the data will be verified, and standard monitoring of the systolic and diastolic blood pressure, mean arterial pressure, pulse rate, electrocardiogram, blood oxygen saturation, entropy index, or bispectral index (BIS) will be conducted. Simultaneously, venous access will be obtained and maintained at a rate of 10–20 mL/kg/h. The total fluid volume will not exceed 50 mL/kg, to ensure intraoperative hemodynamic stability.

Intraoperatively, the same protocol will be used for anesthesia induction: etomidate 0.3 mg/kg or propofol 1.5–2 mg/kg, sufentanil 0.3–0.5 μg/kg, cisatracurium besylate 0.2 mg/kg, or rocuronium bromide 1 mg/kg, respectively. Anesthesia methods, including combined intravenous and inhalation anesthesia, total intravenous anesthesia, inhalation anesthesia, and reasonable use of vasoactive drugs, can be used intraoperatively.

The ventilator will be connected to the participant after a successful tracheal intubation. All participants will be ventilated using lung-protective ventilation, which includes VCV, PCV, and PCV-VG.

The tidal volume will be set at 6–8 mL/kg, which has been calculated, based on the ideal body weight, using the following formulae:For males: 50 + 0.91 × [height (cm)—152.4].For females: 45.5 + 0.91 × [height (cm)—152.4].

Moreover, the positive end-expiratory pressure (PEEP) and inspiratory/expiratory ratio will be maintained at 6–8 cm H2O and 1:2, respectively, with regular lung recruitment maneuvers. The ventilation rate will be adjusted, according to the intraoperative end-expiratory carbon dioxide, which will be maintained at 35–50 mm Hg.

The depth of anesthesia will continuously be adjusted, according to the entropy index, BIS value, or minimum alveolar concentration (MAC) value of the end-expiratory anesthetic gas. The entropy index and BIS value or MAC value of the end-expiratory anesthetic gas will be maintained at 40–60 or 0.7–2.6, respectively.

Intraoperative and perioperative information, adverse events (AEs), and serious adverse events (SAEs) will be recorded. Perioperative data includes the duration of the anesthesia and surgery, use of different types of anesthetics, volumes of fluids administered intraoperatively, and administration of postoperative analgesics and anticholinergic drugs.

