### Criteria for discontinuing or modifying allocated interventions {11b}

The FiO_2_ will be adjusted to 40% and 80% in the L and H cohorts, respectively. Should the intraoperative oxygen saturation of the participants in the L cohort decline to < 94%, while the PEEP remains at 30 cm H_2_O, at a duration of ≥ 30 s, without an improvement in the oxygen saturation, the oxygen concentration will be increased to 80%.

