### Implementation {16c}

A trained research team will recruit participants and use standard randomization procedures, to assign them to the study population on the preoperative day. The anesthesiologist will only be notified of this assignment the day after the participant is admitted to the ward.

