### Methods for additional analyses (e.g., subgroup analyses) {20b}

#### Analysis sets

The enrolled set will consist of all participants who provided informed consent and were added to the study database.The full analysis set (FAS) describes the analysis set, which is as complete and close as possible to the intention-to-treat ideal of including all randomized participants, who have undergone ≥ 1 efficacy assessment, post-randomization.The per-protocol set (PPS) defines a subset of the participants in the FAS who are more compliant with the protocol and have undergone ≥ 1 efficacy assessment, post-randomization. Participants with protocol deviations will be excluded from this analysis.

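### Allocation on the day before surgery, with disclosure timed from ward admission, leaves an avoidable gap before the cohort FiO2 starts; releasing it in theatre would close most of it at low cost

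*Protocol article*

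**What the plan says.** Sequence generation {16a} places allocation on the day before surgery: "The participants will be assigned to two cohorts, as per a 1:1 ratio, on the preoperative day". Who will take informed consent? {26a}, Recruitment {15} and Implementation {16c} repeat this; in the last, the research team will "use standard randomization procedures, to assign them to the study population on the preoperative day".

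Recruitment {15} and Implementation {16c} also control disclosure: "The anesthesiologist will only be notified of this assignment the day after the participant is admitted to the ward". Under Who will be blinded {17a}, the anaesthetist is not blinded.

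On the start of the intervention, Intervention description {11a} says: "The ventilator will be connected to the participant after a successful tracheal intubation". The section on discontinuing or modifying interventions {11b} adds: "The FiO_2_ will be adjusted to 40% and 80% in the L and H cohorts, respectively". The exact moment at which the cohort FiO2 is first set is not stated; that it follows intubation is inferred from these two sections.

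Several choices stay open in Intervention description {11a}. Induction may use either of two hypnotics and either of two relaxants. On maintenance: "Anesthesia methods, including combined intravenous and inhalation anesthesia, total intravenous anesthesia, inhalation anesthesia, and reasonable use of vasoactive drugs, can be used intraoperatively". On ventilation mode: "All participants will be ventilated using lung-protective ventilation, which includes VCV, PCV, and PCV-VG".

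Analysis sets {20b} describes the full analysis set (FAS) as close to the ideal of "including all randomized participants, who have undergone ≥ 1 efficacy assessment, post-randomization". The section on nonadherence and missing data {20c} drops missing primary values, yet also says that all participants will be analysed as randomised.

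**The concern.** Allocation gains nothing from being fixed a day before it is used, and the interval has two costs.

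First, operations are cancelled, postponed or changed in that interval. Those patients have been randomised, but may never receive a cohort FiO2. The article gives no rule for them, and its two statements on who is analysed point in different directions. They become post-randomisation exclusions that later allocation would mostly avoid.

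Second, the one unblinded role that shapes the anaesthetic may learn the cohort before making choices that do not need that knowledge. If the induction agent or anaesthetic method differs by cohort as a result, the comparison is no longer of FiO2 alone.

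**Working it through.** **Order of events, from the sections side by side**

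1. Preoperative day: allocation ({26a}, {15}, {16a}, {16c}).
2. Day after ward admission: the anaesthetist is notified ({15}, {16c}).
3. Day of surgery: induction, intubation, connection to the ventilator ({11a}), FiO2 by cohort ({11b}).

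Step 2 has no fixed place relative to step 3. With admission the day before surgery, notification falls on the day of surgery, possibly before induction. With admission two days before, it falls on the preoperative day. With admission three or more days before, the stated day comes before the allocation exists, so the rule cannot be followed literally.

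**Who is analysed**

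A patient cancelled before induction has no operation, and so no arterial gas at 48 h after it (Primary outcome). With no efficacy assessment the patient does not meet the FAS definition ({20b}). The inclusive sentence in {20c} says otherwise.

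**Size**

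Inputs from Sample size {14}: means 384 and 340 mmHg, so a difference of 44; superiority threshold 30; pooled SD 74; one-sided alpha 0.025; power 80%; dropout 20%.

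The plan's own figure first:

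- n per group = 2 × SD² × (z₀.₉₇₅ + z₀.₈₀)² / (44 − 30)² = 2 × 5476 × 7.849 / 196 = 438.6, rounded up to 439.
- With dropout: 439 / 0.80 = 548.75, rounded up to 549 per group, or 1098 in total.

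Both stated figures reproduce. The dropout allowance is 0.20 × 1098, about 220 people.

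The article gives no cancellation rate, so c = 2% and 5% are assumptions: 0.02 × 1098 = 22 people and 0.05 × 1098 = 55 people.

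- Losses inside the 20% allowance: 439 per group remain and power is 80%.
- Losses on top of it: evaluable per group m = 549 × (1 − c) × 0.80, and power = Φ(14 / (74 × √(2/m)) − 1.96).

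| c | m | power | total N to restore 80% |
|---|---|---|---|
| 2% | 430.4 | 79.3% | 1120 |
| 5% | 417.2 | 78.0% | 1156 |

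The last column is 2 × 439 / (0.80 × (1 − c)), rounded up per group.

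The effect of early knowledge of the cohort cannot be put into figures from the article.

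**The case against.** Randomising on the day before surgery is not in itself an error, and no stated figure is wrong. The article does have a safeguard: it holds the cohort back from the anaesthetist for a time. The assumed 22 to 55 losses fit well within the allowance of about 220. A cancellation decided before any treating clinician knows the cohort should not depend on it, so it costs numbers and does not bias the comparison. Later release would also protect only what happens before FiO2 is set; ventilation, fluids and emergence are still managed by someone who knows the cohort. All of this stands, and it keeps the point small. It does not remove it, because the safeguard is timed from ward admission and so cannot ensure that the cohort is unknown before induction or before a cancellation.

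A reader might infer that unexposed patients stay in the analysis, dilute the 44 mmHg difference and cut power sharply. The article does not support this for cancelled patients: they have no 48-h value and fall outside the FAS. Dilution would need patients who still had surgery and a 48-h gas without the allocated FiO2. The article gives no rate for such patients, and nothing in it says that FiO2 would be withheld from them.

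A reader might also count intraoperative conversion to open surgery as unexposed. Those patients have already been ventilated at the cohort FiO2. Their removal under the rejection criteria in Eligibility criteria {10} is a separate matter.

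**Conclusion.** The point holds as an inexpensive improvement of modest value. Neither allocation nor disclosure is tied to the start of the intervention, so randomised-but-unexposed patients and knowledge of the cohort before induction are both possible. The analysis-set statements in {20b} and {20c} do not agree on the former. The cost in power is nil if losses stay within the planned dropout, and about one to two percentage points if an assumed 2% to 5% come on top. This rests on three things: the assumed rates, the inference that FiO2 is first set by cohort after intubation, and cancelled patients having no 48-h outcome.

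**What to change.** Keep consent and eligibility checks on the preoperative day. Release the EDC allocation in theatre immediately before the cohort FiO2 is set, once the planned laparoscopic operation and the extubation plan are confirmed, by someone who is not an outcome assessor. Amend {26a}, {15}, {16a} and {16c} to match, and replace the notification rule that counts from ward admission.

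This also makes the anaesthetic method, listed as a stratification factor in {16a}, known at allocation. Operative time, listed there too, would still be unknown. The change does nothing for intraoperative conversion to open surgery.

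The cost is a protocol amendment and an EDC log-in in theatre at each of the 16 sites. A change during recruitment would also leave two allocation procedures in one trial, so the date of the switch should be recorded.

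The stated end date is 31 December 2025. If recruitment has closed, leave allocation as it was. Instead, reconcile the FAS definition in {20b} with the inclusive statement in {20c} before any unblinded analysis, and report the number randomised but unexposed in each cohort.

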### Concealment mechanism {16b}

Using a block randomization EDC system for allocation concealment.

### Implementation {16c}

A trained research team will recruit participants and use standard randomization procedures, to assign them to the study population on the preoperative day. The anesthesiologist will only be notified of this assignment the day after the participant is admitted to the ward.

## Assignment of interventions: blinding

### Who will be blinded {17a}

Due to the nature of the study, anesthesiologists will not be blinded to the intervention protocol. Trial participants, outcome assessors, and data analysts will be blinded. To reduce potential bias, data collectors will be divided into two different teams: (1) anesthesiologists on duty in the operating room on the same day, in addition to postanesthetic care unit (PACU) staff, who will participate in the calculation and evaluation of the results, and (2) blinded principal investigator (PI) and co-investigator, statistician, and data collection and outcome evaluation personnel, which includes those who will provide care and evaluate participants in the ward pre- and postoperatively.

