The endotracheal tube will be removed in the operating room. If an endotracheal tube is inserted in the PACU, the ventilator parameters in the PACU should consistently be set intraoperatively, and the endotracheal tube should be removed after rapid recovery of spontaneous breathing. Both cohorts will be given Venturi masks for oxygen inhalation post-extubation, and the FiO2 will be set at 24%–40%. The initial setting will be at 24%. If clinical requirements are not met, the FiO2 will be increased to 40%, as needed. The FiO2 and duration of oxygen inhalation will be recorded.

After returning to the ward, the participants will decide whether to receive supplemental oxygen, based on their present condition. If oxygen is required, a Venturi mask will be used. The total time and concentration of oxygen inhalation will be recorded. Each site can use multimodal analgesia, as per the current condition.

During the postoperative monitoring period, evaluations will be conducted, and data will be documented for both the primary and secondary outcome measures.

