### Outcomes {12}

#### Primary outcome

The primary outcome measure is the comparison of the 48-h postoperative oxygenation index between the two cohorts. This will be derived from arterial blood gas sampling and analysis, in addition to the FiO_2_ 48th h postoperatively.

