## Data collection and management

### Plans for assessment and collection of outcomes {18a}

Each site will administer anesthesia, according to their institutional guidelines. Medication type, dosing, and additional analgesics administered, as per each site’s anesthesia protocol, will be documented, in detail, in the case report form (CRF). A qualified and experienced anesthesiologist will be required to complete the CRF.

Prior to study initiation, researchers will receive training on the study protocol, according to the principles of GCP for clinical trials.

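### The blinding section says outcome assessors are blinded, yet gives unblinded anesthesiologists, with PACU staff, a part in calculating and evaluating the results

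*Protocol article*

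**What the plan says.** In the protocol article, Who will be blinded {17a} makes four statements in one paragraph:

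- On those giving the anesthetic: "anesthesiologists will not be blinded to the intervention protocol".
- On everyone else: "Trial participants, outcome assessors, and data analysts will be blinded".
- The first data-collection team is "anesthesiologists on duty in the operating room on the same day, in addition to postanesthetic care unit (PACU) staff", and its task is given as "who will participate in the calculation and evaluation of the results".
- The second team is the "blinded principal investigator (PI) and co-investigator, statistician, and data collection and outcome evaluation personnel", including those who look after and assess participants on the ward.

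Other sections bear on who produces the outcome data:

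- Primary outcome (under Outcomes {12}), on the 48-h oxygenation index: "This will be derived from arterial blood gas sampling and analysis, in addition to the FiO_2_ 48th h postoperatively".
- Strategies to improve adherence to interventions {11c} has experienced anesthesiologists take the postoperative arterial samples.
- Plans for assessment and collection of outcomes {18a}: "A qualified and experienced anesthesiologist will be required to complete the CRF".
- Plans to promote participant retention and complete follow-up {18b} gives the visits up to day 7 to the data collection and outcome evaluation personnel, who belong to the second team.
- Intervention description {11a}, on participants still intubated in the PACU: "the ventilator parameters in the PACU should consistently be set intraoperatively".

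**The concern.** The two-team split is introduced as a guard against bias. Its wording does the reverse: it gives a share in evaluating results to a team that contains the only people the article declares unblinded. A reader cannot tell from the article whether the blinding of assessors is real.

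The primary outcome is a ratio of two quantities. PaO2 comes from the analyser. FiO2 is recorded by a person, the sample is taken by a person under conditions that person can affect, and someone computes the quotient. If staff who know the allocation handle any of these steps, and the working hypothesis favours 40%, a small differential error is possible. Pulmonary complications within 7 days call for more judgement and would be at least as exposed. The PACU oxygen outcomes in Statistical methods {20a} (duration, concentration, rate) arise in the care of first-team staff.

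**Working it through.** **Textual check.** The contradiction needs no arithmetic.

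1. Anesthesiologists know the allocation ({17a}).
2. The first team consists of on-duty operating-room anesthesiologists and PACU staff, and takes part in calculating and evaluating results ({17a}).
3. From 1 and 2, some people who evaluate results know the allocation.
4. Outcome assessors and data analysts are blinded ({17a}).
5. Statements 3 and 4 conflict. The second team already holds the statistician and the outcome evaluators, so evaluation is assigned twice, once to a team not labelled blinded.

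The status of the PACU staff is an inference. They are not called unblinded, but only the second team is called blinded, and the PACU ventilator instruction in {11a} appears to carry the intraoperative settings over for participants who arrive intubated.

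The other sections do not remove the conflict. {11c} and {18a} name anesthesiologists for sampling and for the CRF without a blinding condition. {18b} points the other way, to the second team.

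**The plan's own figure.** Inputs from Sample size {14}: means 384 and 340 mmHg, margin 30, SD 74, one-sided α 0.025, power 80%, dropout 20%.

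- Distance from the margin: (384 − 340) − 30 = 14 mmHg.
- n per group = 2 × (1.960 + 0.842)² × 74² / 14² ≈ 439, as stated.
- With dropout: 439 / 0.8 = 548.75, so 549 per group and 1098 in total, as stated.

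**Illustration of sensitivity.** The bias sizes below are assumed and do not come from the article.

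- Standard error of the difference: 74 × √(2/439) = 4.995 mmHg.
- With a true difference equal to the 30 mmHg margin and a differential bias b favouring 40%, one-sided error = 1 − Φ(1.960 − b / 4.995).

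| Assumed bias b (mmHg) | One-sided error |
|---|---|
| 0 | 2.5% |
| 2 | 5.9% |
| 5 | 16.9% |
| 10 | 51.7% |

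These figures apply to a test against the 30 mmHg margin, which is what the sample size implies. {20a} describes a t-test and mixed models without stating a shifted null. The formula depends only on b and the standard error, so a test against zero would show the same inflation at a true difference of zero.

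**The case against.** The strongest defence is that the sentence is a slip or merely loose. The split is meant to reduce bias, so a dropped negative is plausible. Since the teams divide data collectors by place of work, the results that the first team handles could also mean operating-room and PACU data only. Either reading may be what was intended. Neither is what is printed, and the article does not choose between them, so the correction is still needed.

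The defence has more force against stronger readings. A reader might infer that the primary outcome is shown to be biased, or that the participant's own anesthesiologist draws the sample and computes the index. The documents do not support that:

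- {17a} and {18b} place ward evaluation through day 7, which includes the 48-h time point, with the blinded team.
- No section says that the first team determines the 48-h index.
- {11c} asks for experience in sampling and does not say whose anesthesiologist samples.
- The CRF sentence in {18a} follows text on anesthetic drugs and may mainly concern intraoperative records. Data management {19} has trained professionals enter all trial data, with a data inspector verifying them.

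A reader might also call the trial open-label. That is wrong: participants, assessors and analysts are stated to be blinded.

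Finally, one might set the effect of a misrecorded FiO2 in a single patient beside the 44 mmHg difference in pilot means. The two are not comparable, because one is an individual error and the other a difference between group means. With assumed values of PaO2 80 mmHg and FiO2 0.24 recorded for 0.28, the individual shift is 80/0.24 − 80/0.28 = 47.6 mmHg. A 5 mmHg shift in an arm mean would need about 5/47.6, or roughly one in ten, of that arm misrecorded in the same direction. The article gives no evidence of this.

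**Conclusion.** The contradiction within {17a} stands and should be corrected. As written, unblinded anesthesiologists, together with PACU staff who are not labelled blinded, may take part in evaluating outcomes that the same paragraph says are assessed blind.

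The consequence for the 48-h oxygenation index is a risk of unknown size, confined to the recorded FiO2, the sampling and the calculation of the ratio. The error rates of about 6%, 17% and 52% show only how little room there is beside a standard error of 5.0 mmHg. They rest on assumed biases of 2, 5 and 10 mmHg, on 439 evaluable participants per group and on a test against the 30 mmHg margin. They do not estimate what will happen in this trial. The sample size is unaffected.

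**What to change.** In {17a}, delete the clause that lets the first team calculate and evaluate results, or state that it takes no part in either. Limit that team to delivering the intervention and recording intraoperative and PACU data.

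State that the blinded second team records the 48-h FiO2, calculates the index and assesses complications. State that the 48-h arterial sample is drawn by an experienced anesthesiologist who was not involved in that participant's operation, which keeps the sampling skill that {11c} asks for. Align {11c} and {18a} with this, making clear in {18a} which parts of the CRF the anesthesiologist completes.

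Report the PACU oxygen outcomes as recorded by staff who may know the allocation.

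The cost is a change of text and of role assignments, using a blinded team that already exists. The downside is minor rota planning for the 48-h sample. If samples or assessments have already been obtained, the trial team should document who performed them.
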